### Adverse event reporting

2.9

#### Adverse events and serious adverse events

2.9.1

Adverse events (AEs) are defined as undesirable and unintended signs, symptoms, or diseases that occur in participants during a clinical trial, regardless of whether they are causally related to the investigational treatment. AEs are identified through vital sign measurements, participant self-reports, investigator observations, and AE monitoring. Any clinically significant symptoms or changes, as determined by the investigator, are considered AEs and must be documented in the case report form, including details of occurrence, evaluation, and management. Medical events that occur before the administration of the investigational product are documented as medical history, while AEs occurring after trial completion are reported only if they are classified as serious and deemed related to the investigational product.

Serious adverse events (SAEs) are defined as any AE occurring at any dose of the investigational product that results in one or more of the following: (1) death or life-threatening events, (2) hospitalization or prolonged hospitalization, (3) permanent or significant disability/incapacity, (4) congenital anomaly or birth defect, or (5) other medically important conditions, such as drug dependence or abuse, blood disorders, or other significant medical events.

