The ground truth (target variable) for model training was the observed change in the Gastrointestinal Symptom (GIS) score from baseline to 8 weeks in the preliminary study. The models were trained using comprehensive baseline data as input features. These features included demographics (e.g., age, sex, and FD duration); patient-reported outcomes and questionnaires (e.g., GIS, and various pattern identification questionnaires); data from Korean medicine diagnostic devices (e.g., tongue diagnosis system, radial pulse analyzer, and digital algometer readings); and laboratory test results (e.g., blood chemistry).

During development, the dataset was split into training (80%) and test (20%) sets for internal validation. Hyperparameter tuning was conducted using RandomizedSearchCV with 5-fold cross-validation on the training data. To mitigate overfitting due to high data dimensionality, an iterative feature selection process was employed to enhance model robustness. The final models demonstrated robust predictive accuracy on the independent test set, confirming their capability to predict treatment responses and discriminate the relative effectiveness among the herbal formulations. Detailed methodology of the algorithm development is provided in Supplementary material 1. The algorithm for prediction system employed in this trial is a locked version (v1.1) that will not be updated during the study period. The prospective validation of this locked algorithm in a new cohort is essential for evaluating its generalizability and mitigating potential biases or overfitting inherent in the preliminary training dataset.

All groups will take the assigned clinical trial medications for 8 weeks. Participants will attend clinic visits at 4-week intervals until week 8 for evaluation of clinical variables, including vital signs, questionnaire surveys, and assessments with Korean medicine diagnostic devices (heart rate variability [HRV], tongue diagnosis, pulse diagnosis, and abdominal diagnosis). In addition, telephone visits will be conducted at 2-week intervals (weeks 2 and 6) to assess whether FD-related pain or discomfort has moderately improved since the previous treatment (Figure 1). Before and after taking the herbal medicine, blood samples (at screening and week 8) and stool and saliva samples (at weeks 0 and 8) will be collected to analyze blood and fecal metabolites as well as gut and oral microbiomes. A detailed assessment schedule is provided in Table 1.

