**Figure 1 fig1:**
[figure not shown]
Flowchart of the trial intervention. ML, machine learning; YJT, *Yijung-tang*; PWS, *Pyeongwi-san*; SST, *Shihosogan-tang*; GIS, gastrointestinal symptom.

**Table 1 tab1:** Clinical study schedule.

Assessment	Visit 1 (screening)	Visit 2 (baseline, week 0)	Visit 3 (week 2)	Visit 4 (week 4)	Visit 5 (week 6)	Visit 6 (week 8)
Written consent						
Demographic/medical history survey	●					
Physical measurements	●					
Vital sign measurements	●	●		●		●
Blood test	●					
Confirmation of inclusion / exclusion criteria	●					●
Random allocation		●				
Concomitant medications and adverse reaction confirmation		●	●	●	●	●
Gastrointestinal Symptom Score	●			●		●
Total Dyspepsia Symptom Score	●			●		●
Adequate relief of dyspepsia			●	●	●	●
Overall treatment effect				●		●
Dyspepsia Visual Analog Scale	●			●		●
Functional dyspepsia–related quality of life	●			●		●
Spleen Qi Deficiency Questionnaire	●			●		●
Stomach Qi Deficiency Questionnaire	●			●		●
Food Retention Questionnaire	●			●		●
Cold–Heat Pattern Questionnaire	●			●		●
Deficiency–Excess Pattern Questionnaire	●			●		●
Standard Tool for Pattern Identification of FD	●					
Korean medicine diagnosis (interview, tongue, pulse, abdominal)	●			●		●
Clinical trial medication prescription and administration education		●		●		
Clinical trial medication returns and compliance check				●		●
Stool kit and meal record sheet provision	●			●		
Stool sample collection, meal record sheet confirmation, and saliva sample collection		●				●
Confirmation of clinical study completion						●

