#### Predictable adverse events and precautions

2.9.2

Adverse reactions that cannot be excluded as causally related to the investigational intervention are considered predictable AEs. In a previous study (30), patients with FD received either Western medicine alone or in combination with YJT for 4 weeks. The combination group reported diarrhea (2 cases), abdominal pain (3 cases), dizziness (1 case), and headache (1 case). In the Western medicine group, diarrhea (2 cases), abdominal pain (1 case), dizziness (1 case), and headache (1 case) were reported. There was no statistically significant difference in AE incidence between groups, and no SAEs were reported in either group. Furthermore, an eight-week clinical trial of modified PWS reported no treatment-related AEs (31). According to clinical practice guidelines for FD (10), six randomized controlled trials reported fewer AEs with SST compared to prokinetic agents (RR 0.32, 95% CI 0.14–0.78). Possible AEs in the present trial include bruising or subcutaneous bleeding from blood draws, rare cases of phlebitis secondary to infection, and transient discomfort or pain associated with abdominal pressure.

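### Harm from the screening blood draw or abdominal examination would be filed as medical history, although the protocol's own definition and list make it an adverse event

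*Protocol article*

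**What the plan says.** Section 2.9.1 defines AEs as unwanted "signs, symptoms, or diseases that occur in participants during a clinical trial, regardless of whether they are causally related to the investigational treatment". Later in the same paragraph comes the recording rule: "Medical events that occur before the administration of the investigational product are documented as medical history". An SAE is then defined as an AE, at any dose of the study product, that meets one of the listed seriousness criteria.

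Section 2.9.2 reviews earlier safety data on the three formulas and closes with the harms expected here: "Possible AEs in the present trial include bruising or subcutaneous bleeding from blood draws, rare cases of phlebitis secondary to infection". It adds short-lived soreness from pressing on the abdomen.

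On timing, Section 2.1.1 puts laboratory tests and the Korean medicine device assessments in the screening visit, with randomisation within 2 weeks of it. It schedules "blood samples (at screening and week 8", and Section 2.5.3 gives the same two times for the liver and kidney tests. Table 1 marks the Korean medicine diagnosis, which includes the abdominal examination, at Visits 1, 4 and 6. It marks the medical history survey at Visit 1 only. It marks "Concomitant medications and adverse reaction confirmation" from Visit 2, the visit at which study medication is first prescribed.

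**The concern.** The definition, the recording rule, the list of possible harms and the schedule do not agree for one class of event: harm caused by a study procedure between consent and the first dose. Phlebitis after the screening draw is an AE by definition and a named possible AE of this trial, yet it is medical history under the recording rule.

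Two things follow. A harm that the trial caused is entered as though the participant had brought it along. And a serious procedural event before dosing falls outside the SAE wording, because that wording presupposes both an AE and a dose. Section 2.10 sets up no data monitoring committee and relies on the investigators and the study team, so the definitions decide what enters the safety record.

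**Working it through.** The protocol states no figure on this point, so there is nothing to reproduce. The check has two parts.

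**1. One event followed through the text.** Take a participant who consents, has blood drawn at screening and develops phlebitis before dosing.

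- Definition in Section 2.9.1: the event occurs during the trial and cause is irrelevant, so it is an AE.
- List in Section 2.9.2: phlebitis from blood draws is named, so it is an expected AE.
- Recording rule in Section 2.9.1: it precedes the first dose, so it is medical history.
- Table 1: the history survey is marked only at Visit 1, so an event arising afterwards has no scheduled history entry. The Visit 2 check can detect it, but the recording rule bars it from being labelled an AE.
- SAE definition in Section 2.9.1: if the event were serious, it would be neither an AE under the recording rule nor at a dose, so it would not be classed as an SAE.

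**2. How many procedure occasions are exposed to the rule.** The inputs are blood draws at screening and week 8 (Sections 2.1.1 and 2.5.3), abdominal examinations at screening, week 4 and week 8 (Table 1), and 100 participants with 10% dropout (Section 2.7). I assume that dropout applies to every post-baseline visit, which makes 90 attenders at each.

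Share before dosing = pre-dose occasions / all occasions.

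| Procedure | No dropout | 10% dropout |
|---|---|---|
| Blood draw | 100/(100 + 100) = 50% | 100/(100 + 90) = 53% |
| Abdominal examination | 100/(100 + 200) = 33% | 100/(100 + 180) = 36% |
| Both | 200/500 = 40% | 200/470 = 43% |

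So about 60% of occasions (57% with dropout) come after the first dose, and harms from those remain countable as AEs. People who have the screening procedures but are never randomised would add only pre-dose occasions. Their number is not given, so they are left out.

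**The case against.** Filing pre-dose events as history is a common convention for treatment-emergent reporting. Screening procedures precede randomisation and are the same for both arms. The only between-group AE test in Section 2.8.3 covers medication-related events, which a pre-dose event cannot be. The named harms are mostly minor, and a journal article may leave detailed recording instructions to the full protocol. All of this limits the consequence. It does not remove the conflict, because the article states the rule outright and without exception, next to a definition and a list that contradict it. The convention settles what may be attributed to the drug. It does not settle where harm from the trial's own procedures is recorded.

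A reader might infer more than the text supports:

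- *That the predicted harms arise only at screening.* They do not. The procedures are repeated on treatment, and Section 2.9.2 also cites drug-type events from an earlier study: "The combination group reported diarrhea (2 cases), abdominal pain (3 cases), dizziness (1 case), and headache (1 case").
- *That screening harms would go unseen.* The Visit 2 check can pick them up in participants who reach that visit. The fault is in the label.
- *That worsening on treatment would be missed.* Section 2.9.1 counts clinically significant changes, as judged by the investigator, as AEs.
- *That pre-dose SAEs would get no review.* Section 2.10 gives the investigators ongoing safety monitoring with no start date, and Section 2.11 covers injury from participation without reference to dosing. The classification is unclear, but nothing says that such events go unreviewed.
- *That all blood draws precede dosing.* Table 1 as extracted marks the blood test at screening only. The text gives a week 8 draw in two places, and the missing mark may be an extraction fault.
- *That half of venepuncture harms and a third of abdominal-pressure harms are misfiled.* Those would be shares of occasions turned into harms by assuming equal risk per procedure, for which the document gives no data.

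**Conclusion.** The inconsistency is real and narrow. As written, harm from the screening blood draw or the screening abdominal examination, including any serious harm, is recorded as medical history and drops out of the descriptive AE and SAE counts. Section 2.8.3 promises frequencies of events both related and unrelated to the intervention, and that output would be incomplete.

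The exposure is 1 of 2 blood draws and 1 of 3 abdominal examinations per completer, in a window of up to 2 weeks before randomisation. The number of harms lost cannot be estimated from the document. The comparison of medication-related AEs between ACCORD and DISCORD is not biased, and no efficacy analysis is touched. The conclusion rests on reading the recording rule literally and on taking the blood-draw times from the text and not from Table 1.

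**What to change.** Reconcile Sections 2.9.1 and 2.9.2 with Table 1:

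- State in Section 2.9.1 that study-procedure-related AEs and all SAEs are recorded from written consent, and word the SAE definition so that it does not depend on a dose having been taken.
- Limit medical history to conditions present before consent and to unrelated, non-serious events before the first dose.
- State that the Visit 2 check covers events since screening.
- Report pre-dose events on a separate line, so that the on-treatment table and the between-group comparison stay as planned.

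The cost is a sentence or two in Section 2.9.1, a note to Table 1, a pre-dose/on-treatment flag in the eCRF, and a few extra minor events to record. Sample size and efficacy analysis do not change.

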#### Predictable adverse events and precautions

2.9.2

Adverse reactions that cannot be excluded as causally related to the investigational intervention are considered predictable AEs. In a previous study (30), patients with FD received either Western medicine alone or in combination with YJT for 4 weeks. The combination group reported diarrhea (2 cases), abdominal pain (3 cases), dizziness (1 case), and headache (1 case). In the Western medicine group, diarrhea (2 cases), abdominal pain (1 case), dizziness (1 case), and headache (1 case) were reported. There was no statistically significant difference in AE incidence between groups, and no SAEs were reported in either group. Furthermore, an eight-week clinical trial of modified PWS reported no treatment-related AEs (31). According to clinical practice guidelines for FD (10), six randomized controlled trials reported fewer AEs with SST compared to prokinetic agents (RR 0.32, 95% CI 0.14–0.78). Possible AEs in the present trial include bruising or subcutaneous bleeding from blood draws, rare cases of phlebitis secondary to infection, and transient discomfort or pain associated with abdominal pressure.

### Monitoring

2.10

Monitoring of this clinical study will be conducted to ensure compliance with the IRB-approved protocol, Good Clinical Practice (GCP) guidelines, and applicable regulatory requirements. Monitoring will be performed either through on-site visits to the clinical trial sites or via telephone by monitors designated by the Korea Institute of Oriental Medicine.

A key component of monitoring is Source Data Verification (SDV). Monitors will systematically validate the survey results and other data entered into the eCRF by comparing them against the original source documents (e.g., medical records, original patient-reported outcome records). Any discrepancies will be managed through a formal data query process until resolved.

The monitoring process includes an initiation visit, routine monitoring visits, and a close-out visit. The initiation visit will occur within 3 weeks after enrollment of the first participant. Routine monitoring visits will be scheduled according to the pace of participant recruitment, and the close-out visit will be conducted after completion of the final participant visit.

Given the established safety profile of the investigational products (YJT, PWS, and SST), which are approved and widely used in Korean medicine, an independent Data Monitoring Committee (DMC) will not be constituted. Instead, the Principal Investigators and the study team will be responsible for ongoing safety monitoring. All Serious Adverse Events (SAEs) will be reviewed immediately upon report.

Independent audits may be conducted by regulatory authorities or the sponsor (National Research Foundation of Korea) to ensure GCP compliance, independent of the routine monitoring activities.

### Ethical considerations

2.11

The study protocol was reviewed and approved by the IRB of Kyung Hee University Hospital at Gangdong on 9 June 2025 (IRB no. KHNMCOH 2025–04–010-001) and by the IRB of Dongguk University Ilsan Oriental Medical Hospital on 10 June 2025 (IRB no. DUIOH 2025–03–004-005). The protocol has been registered on the Clinical Research information Service (CRiS, registration number: KCT0010587) and the Open Science Framework.^1^ All study-related information will be provided to each participant, and written informed consent will be obtained. The study will adhere to the Declaration of Helsinki and GCP guidelines, and be complied with the Standard Protocol Items: Recommendations for Interventional Trials (SPIRIT; Supplementary material 2).

All personal information collected from potential and enrolled participants will be kept strictly confidential. Each participant will be assigned a unique study identification number, and all data will be recorded and analyzed using this code without direct identifiers. Personal identifiers (e.g., name, address, phone number) will be stored separately in a password-protected file accessible only to the principal investigator and authorized research staff. No identifying information will be disclosed in study reports or publications.

Any substantial modifications to the study protocol (e.g., changes in eligibility criteria, outcomes, or analyses) will be documented in a formal amendment. Such amendments must be approved by the IRBs of both institutions before implementation and updated on the clinical trial registries (CRiS and OSF).

Participants will be covered by clinical trial insurance in accordance with local regulations. In the event of any injury resulting directly from participation in the study, appropriate medical care will be provided, and compensation will be offered as determined by the insurance policy and institutional guidelines.

The results of this study, whether positive, negative, or inconclusive, will be disseminated through publication in a peer-reviewed scientific journal and presentations at relevant national or international conferences. Authorship eligibility will follow the guidelines of the International Committee of Medical Journal Editors (ICMJE).

## Discussion

3

This clinical trial is a randomized, assessor-blind, parallel, open-label, multi-center study designed to evaluate the predictive accuracy of a machine learning-based herbal medicine response prediction algorithm in patients with FD. Participants are prospectively assigned to receive YJT, PWS, or SST either based on the machine learning–driven prediction algorithm or without the guidance. The predictive performance of the algorithm will be assessed over an eight-week treatment period.

The etiology of FD is heterogeneous and multifactorial, involving gastrointestinal motility disorders, visceral hypersensitivity, immune activity, barrier dysfunction, genetic predisposition, and alterations in the gut microbiota (4). Additionally, psychological factors such as anxiety, depression, somatization, and stress have been shown to influence FD (3). These complex and interrelated mechanisms underscore the need for innovative approaches such as AI to enhance the precision and personalization of treatment strategies.

This study represents an important step forward in applying AI to traditional Korean medicine, particularly for the management of FD. By integrating AI into traditional practice, the study aims to bridge the gap between subjective diagnostic methods and objective, data-driven approaches. The ability of AI to analyze complex datasets and predict individual responses to herbal treatments offers a promising means of addressing the multifactorial challenges of FD. The potential of AI to refine treatment strategies and improve patient outcomes underscores its value as a transformative tool in personalized medicine.

Recent studies have highlighted the potential of AI to revolutionize the diagnosis and treatment of FD. Researchers have developed AI models to differentiate FD from healthy conditions using diverse data sources, including medical imaging and neurological responses (32, 33). These findings suggest that AI-assisted diagnostic tools may enhance both the accuracy and feasibility of FD diagnosis. Furthermore, research efforts are underway to apply AI to pattern identification in FD (34). Machine learning techniques are being used to analyze multiple symptoms and signs, enabling the identification of key indicators that distinguish between different FD patterns. Such approaches underscore AI’s role in refining diagnostic criteria and enhancing the reliability of pattern identification tools, thereby contributing to more accurate and individualized treatment strategies for FD.

Despite these promising advancements, current machine learning models applied to FD face several limitations. Such models depend heavily on large and diverse datasets for training; however, these datasets are often difficult to obtain and may not fully capture the heterogeneity of FD across different populations. This limitation raises concerns regarding the generalizability of AI-driven diagnostic tools. Furthermore, many machine learning models are developed under controlled research conditions but may encounter challenges when implemented in real-world clinical practice, where variability in data quality and patient demographics can substantially affect performance. The multifactorial nature of FD—encompassing gastrointestinal motility disorders, visceral hypersensitivity, and psychological influences—also complicates predictive modeling, as machine learning frameworks typically excel in identifying patterns within more straightforward datasets. Additionally, there is a risk of algorithmic bias, whereby AI-based systems may inadvertently prioritize certain symptoms or demographic groups, potentially skewing diagnostic accuracy and treatment outcomes. These challenges underscore the need for continued refinement of machine learning approaches and rigorous validation of AI applications across diverse clinical settings to ensure both efficacy and reliability.

Beyond the algorithmic challenges, the inherent heterogeneity of FD also poses implications for the statistical analysis of this trial. Given the substantial heterogeneity of FD, the present study was powered for the overall primary comparison (ACCORD vs. pooled DISCORD). Therefore, any subgroup findings should be interpreted cautiously due to limited power after sample fragmentation. Future studies specifically designed and powered to evaluate differential effects in clinically relevant subpopulations are warranted to fully address these complexities.

The decision to exclude a physician-based control group is supported by the current clinical consensus and the inherent challenges in traditional diagnostic practices. According to the Korean Medicine Clinical Practice Guideline for Functional Dyspepsia [10], herbal medicine treatment is primarily guided by Pattern Identification. However, the guideline explicitly states that “evidence for selecting standardized tools to diagnose and evaluate Pattern Identification is currently lacking,” highlighting the difficulty in establishing a standardized diagnostic protocol [10]. It further notes that the personalized nature of diagnosis, which depends heavily on individual patient characteristics and clinician experience, poses a challenge to standardization. Consequently, employing ‘physician’s choice’ as a comparator in this validation phase could introduce substantial inter-physician variability, acting as a confounding factor that obscures the assessment of the machine learning algorithm’s intrinsic predictive accuracy. Despite this methodological rationale, we acknowledge that a significant limitation of this study lies in the design of the control group regarding the interpretation of clinical utility. The DISCORD group, which receives a treatment predicted as suboptimal by the algorithm, does not represent the standard of care (i.e., physician’s choice). While this design is appropriate for validating the predictive accuracy of the model, it cannot demonstrate the superiority of the algorithm over current clinical practice. Consequently, the observed effect size may be larger than what would be observed in a pragmatic trial comparing algorithm-guided treatment to physician’s choice. Future studies comparing the algorithm against standard care are required to establish its real-world clinical utility.

In conclusion, this study marks an important advancement in applying AI to traditional Korean medicine, offering a more personalized and effective approach to the management of FD. By continuing to explore the intersection between technological innovation and traditional practices, the scientific rigor and global credibility of Korean medicine can be further strengthened. Future research should expand the applicability of AI-driven strategies across diverse populations and investigate long-term outcomes to fully realize the potential benefits of this innovative approach.

